## Abstract

**Background:**

Cardiovascular disease is the leading cause of mortality worldwide. Risk factors associated with cardiovascular disease have been shown to track from childhood through to adulthood. Previous school-based physical activity interventions have demonstrated modest improvements to cardiovascular disease risk factors by implementing extra-curricular activities or improving current physical education curriculum. Few have attempted to increase physical activity in class-room taught curriculum subjects. This study will outline a school-based cross-curricular physical activity intervention to combat cardiovascular disease risk factors in 11-14 year old children.

**Method/Design:**

A South Wales Valley school of low socio-economic status has been selected to take part. Participants from year eight (12-13 years) are to be assigned to an intervention group, with maturation-matched participants from years seven (11-12 years) and nine (13-14 years) assigned to a control group. A cross-curricular physical activity intervention will be implemented to increase activity by two hours a week for 18 weeks. Participants will briskly walk 3200 m twice weekly during curriculum lessons (60 minutes duration). With the exception of physical education, all curriculum subjects will participate, with each subject delivering four intervention lessons. The intervention will be performed outdoors and on school premises. An indoor course of equal distance will be used during adverse weather conditions. Cardiovascular disease risk factors will be measured pre- and post-intervention for intervention and control groups. These will take place during physical education lessons and will include measures of stature, mass, waist, hip, and neck circumferences, together with skinfold measure's taken at four sites. Blood pressure will be measured, and fitness status assessed via the 20 m multi-stage fitness test. Questionnaires will be used to determine activity behaviour (physical activity questionnaire for adolescence), diet (seven day food diary) and maturation status. Fasting blood variables will include total cholesterol, low-density lipoprotein cholesterol, high density lipoprotein cholesterol, triglycerides, insulin, glucose, high-sensitivity C-reactive protein, interleukin-6, adiponectin, and fibrinogen. Motivational variables and psychological well-being will be assessed by questionnaire.

**Discussion:**

Our study may prove to be a cost effective strategy to increase school time physical activity to combat cardiovascular disease risk factors in children.

**Trial Registration:**

[NCT00998478]

## Background

Cardiovascular disease (CVD) is the leading cause of mortality worldwide [1]. In 2005 there was a reported 17.5 million deaths related to the disease, representing 30% of the global population [2]. Risk factors for CVD including obesity, blood pressure, blood lipids and lipoproteins have shown to track from childhood through to adulthood [3,4]. Metabolic syndrome (MetS) is the co-existence of multiple risk factors including hyperinsulinaemia, glucose intolerance, hypertension, decreased levels of high-density lipoprotein cholesterol (HDL-C) and elevated triglycerides (TG) [5]. At least one MetS risk factor was evident in one third of children (12-19 years) from the Third National Health and Nutritional Survey [6]; whereas one in ten was diagnosed with the syndrome itself when using the National Cholesterol Education Programme - Third Adult Treatment Panel definition. The prevalence of overweight and obesity for children (4-18 years) in the UK is reported to be 15 and 4% respectively [7]. Furthermore, in comparison to England (2.9%) obesity was more prevalent for those living in Scotland (7.6%) and Wales (6.5%).

For many, overweight and obesity is the result of the combined effect of excess energy consumption and inadequate physical activity (PA) [8]. Previously, for children and adolescents PA has correlated negatively with body fatness and insulin resistance [9-11]. Conclusions regarding associations with blood lipids and lipoproteins are less clear. Although a recent meta-analysis reported no effect of aerobic exercise on non-high-density lipoprotein cholesterol, further studies are warranted [12]. Despite this, significant inverse relationships between PA and metabolic risk scores have recently been reported [13,14], highlighting the importance of PA on childhood health. Schools are thought to be the ideal setting to implement PA interventions to combat CVD risk factors, with access to large populations from a variety of social classes, coinciding with a monitoring structure already in place [15,16].

The association between psychosocial variables and obesity is complex. Research findings in this area indicate that there is a relationship between depression in youth and subsequent obesity [17,18]. The stigma attached to being overweight may affect peer relationships and may result in children and adolescents feeling less able to participate in PA and more likely to suffer from psychological distress [19,20].

The impact of PA on psychological health and well being has been noted for some years. Biddle et al. [21] reported that PA was associated with reduced levels of anxiety and depression and improved self-esteem, mood and cognitive function. In addition, epidemiological evidence suggests that PA is associated with a decreased risk of developing depression [22]. Exercise programmes have consistently been found to be as effective in reducing levels of depression in adult samples as a variety of standard psychotherapeutic treatments [23].

The relationship between PA and psychological well-being needs further investigation. Physical activity can have a positive effect on self-esteem and physically active children tend to suffer from fewer mental health problems [24]. In a review of PA in children and adolescents, Biddle et al. [25] suggest that a lack of PA in children has been associated with a number of psychosocial variables and perceived barriers. Positive effects on self-esteem are evident for all people participating in PA however the impact on self-perceptions is particularly strong for children [26]. A different pattern of psychosocial variables seems to be important for adolescents including perceived competence, and achievement orientation.

Previous school-based interventions targeting both children and adolescents have demonstrated modest improvements to CVD risk factors, including obesity, insulin resistance, blood pressure, and blood lipids [15,27-29]. Many of these school-based interventions have also looked to improve diet. Most school-based PA interventions have looked to improve physical education (PE) lessons or to provide extra-curricular activities [15,30,31]; few studies have sought to increase PA levels by integrating exercise into what would normally be classroom delivered subjects.

Recently an intervention by Reed et al. [32] used a whole school approach targeting six action zones to increase elementary school children's (9-11 years) PA. The only prescriptive component was to introduce three 15-minute periods per week of classroom PA. This allowed participants to carry out activities including skipping, dancing and resistance exercises. Sixteen months into the programme, improvements in aerobic fitness and blood pressure were evident, but no effect was observed for blood lipids, apolipoprotein B, C-reactive protein, and fibrinogen. Despite detail pertaining to the duration of time provided for participants to perform PA, there was no information regarding the amount of actual PA performed. It is evident that more population-based prevention programs are needed [33]. Targeting class-room based curriculum subjects with an increase in PA, may display favourable outcomes in child CVD risk status.

## Method/Design

### Objectives

This study aims to implement an 18-week school-based cross-curricular exercise intervention to improve CVD risk status, psychological well-being, and motivation to exercise in 12 to 14 year old children.

### Primary Objectives

1. Reduce measures of obesity including body mass index (BMI), waist, hip, and neck circumferences, and total skinfold thickness.

2. Reduce systolic and diastolic blood pressure.

3. Improve aerobic fitness profiles and increase PA behaviour.

4. Improve blood lipid profiles and lower levels of plasma inflammatory markers.

5. To assess the impact of motivation to exercise on physiological and psychological outcomes following the cross-curricular intervention

6. To influence psychological well being (mood and negative affect), self concept, and cognitive performance in an intervention group compared with a control.

### Secondary Objectives

Determine associations between CVD risk factors measured at baseline in 11-14 year old children and adolescents. To investigate the relationships between specific physiological and psychological changes between and within participants.

### Participants

A South Wales Valley school of low socio-economic status (SES) has been selected to take part. Free school meal eligibility was used to ascertain a valid measure of SES [34]. Of all 11-16 year olds attending the school, a reported 28% are eligible for free school meals which is above the unitary authority average of 25% [35]. Following an explanation of the study's aim to the school's headmaster, gatekeeper consent has been granted for participants from years seven (11-12 years), eight (12-13 years), and nine (13-14 years) to take part. Participants from year eight will be assigned to an exercise intervention; maturation matched participants from years seven and nine will form a control group. A member of the research team will outline the study to all children from years seven, eight, and nine during the relevant school assemblies. This will be followed by the distribution of appropriate information sheets together with consent forms. Written consent and assent will be required from both parent/guardian and child respectively for participation in the study. A favourable opinion was provided by the Dyfed Powys Research Ethics Committee for this project.

### Data Analysis

A quasi-experimental design will be used to compare differences in measured outcomes between pupils assigned to an intervention or control group. Initially, baseline data will be used to perform pearson's product moment correlation coefficients, followed by multiple regression analysis to estimate the significance of selected predictors on CVD risk factors. Dependant t-tests will be employed to assess differences between measures taken at baseline and post-intervention with independent t-tests utilised to detect differences in variables between groups. Statistical significance will be set at *P *≤ 0.05. Power calculations revealed that 100 participants from the exercise group and 60 participants from the control were required to achieve 80% power.

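### The stated t-tests do not give a clear test of the intervention: paired tests cannot separate it from growth, and the independent t-test is unadjusted and does not say whether it uses post values or change

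*Protocol article*

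**What the plan says.** The Data Analysis section sets out the tests in one sentence: "Dependant t-tests will be employed to assess differences between measures taken at baseline and post-intervention with independent t-tests utilised to detect differences" between groups. The between-group part reads in full "independent t-tests utilised to detect differences in variables between groups", which leaves open which variable is compared: the post value, the change, or something else. The only multivariable model belongs to the cross-sectional baseline analysis: "baseline data will be used to perform pearson's product moment correlation coefficients, followed by multiple regression analysis". No baseline value, sex, age or maturation stage is named for the intervention effect.

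On the groups, the Participants section says: "Participants from year eight will be assigned to an exercise intervention; maturation matched participants from years seven and nine will form a control group". The Abstract gives the ages as 12-13 for year eight, 11-12 for year seven and 13-14 for year nine. The Discussion admits the lack of randomisation as a main limitation, but attaches no analytic remedy to it.

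The first primary objective is "Reduce measures of obesity including body mass index (BMI), waist, hip, and neck circumferences, and total skinfold thickness". Blood pressure and aerobic fitness follow. All are measured before and after 18 weeks in both groups (Measurements), and maturation stage is collected by self-report (Questionnaires). On size, the plan says: "Power calculations revealed that 100 participants from the exercise group and 60 participants from the control were required to achieve 80% power".

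**The concern.** Girths, BMI, blood pressure and shuttle-run score can all be expected to drift in children of 11 to 14 over 18 weeks, whatever the intervention does. A pre/post test within one group measures that drift and any effect together. A between-group test is the right kind of comparison, but allocation by school year gives no assurance that the groups start level. On post values, a starting difference is counted as effect. On change, a different growth rate or regression to the mean is counted as effect.

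These are the only tests of the intervention that the article states. An analyst could follow the text faithfully with either version of the independent t-test and reach different answers for the same outcome.

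**Working it through.** **Inputs from the article.** 100 intervention and 60 control pupils, 80% power, significance level 0.05 (Data Analysis). Sidedness is not stated; two-sided is assumed.

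**Assumed inputs, not in the article.** Pre-post correlation r, baseline gap, growth drift and differential growth, all in SD of the outcome and shown over a range.

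**1. The plan's own figure.** No outcome, effect size or SD is given, so 100 and 60 cannot be reproduced, only solved backwards.
- Standard error of a difference in means, in SD units: sqrt(1/100 + 1/60) = 0.1633.
- Detectable difference: (1.960 + 0.842) × 0.1633 = 0.457 SD, or 0.460 SD with the t distribution. Below, 0.46 SD is used.

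**2. Paired test, no intervention effect.** SD of change = sqrt(2(1 − r)). With an assumed growth drift of 0.1 SD, the noncentrality is 0.1 × sqrt(n) / sqrt(2(1 − r)).

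| r | rejects, n = 100 | rejects, n = 60 |
|---|---|---|
| 0.7 | 25% | 17% |
| 0.8 | 35% | 23% |
| 0.9 | 60% | 40% |

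The nominal rate is 5%. The rate measures growth, and it differs between the groups through their size alone.

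**3. Independent t-test on post values, no effect, baseline gap 0.2 SD.**
- Gap regresses towards a common mean, r = 0.8: shift 0.2 × 0.8 = 0.16 SD; 0.16/0.1633 = 0.98; rejects 16.4%.
- The same with r = 0.9: shift 0.18 SD; 0.18/0.1633 = 1.10; rejects 19.5%.
- Gap persists in full: shift 0.20 SD; 0.20/0.1633 = 1.22; rejects 23%.

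With a persisting gap of only 0.1 SD the rate is 9%.

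**4. Independent t-test on change, no effect.**
- Parallel growth and a fixed gap: both cancel, and the test rejects 5% of the time.
- Growth differing between groups by 0.1 SD: noncentrality 0.1 / (sqrt(2(1 − r)) × 0.1633); rejects 16% (r = 0.8) or 28% (r = 0.9).

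**5. Precision.** The detectable difference is 0.46 × sqrt(1 − r²) with baseline adjustment and 0.46 × sqrt(2(1 − r)) for change.

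| r | post-value t-test | t-test on change | baseline-adjusted |
|---|---|---|---|
| 0.5 | 0.46 | 0.46 | 0.40 |
| 0.8 | 0.46 | 0.29 | 0.28 |
| 0.9 | 0.46 | 0.21 | 0.20 |

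Baseline adjustment gains much over post values, and little over change when r is high.

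**6. Limit of the remedy.** If a 0.2 SD gap is stable, baseline adjustment leaves a bias of 0.2 × (1 − r): 0.04 SD at r = 0.8 and 0.02 SD at r = 0.9. The change score leaves none. If the gap regresses instead, the roles reverse. The data cannot say in advance which holds, which is why both analyses belong in the report.

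**The case against.** A reader might infer that the investigators will take growth or baseline differences for intervention effects, or will judge the trial by significance in one group and not in the other. The article says neither. The Data Analysis section opens by making the comparison between groups the aim, and nothing states how the paired results will be interpreted. The point is that those tests cannot serve as evidence of effect, not that they will be used so.

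The independent t-test may well be meant for change scores. Shared growth and a fixed gap would then cancel, and little precision would be lost at high r. That stands, and it narrows the concern to differential growth and regression to the mean. It does not remove it, because the text does not fix that reading.

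The design also answers part of the growth problem: controls are matched on maturation, and years seven and nine bracket year eight in age. This counts in the plan's favour. But matching on self-reported stage does not balance baseline outcomes, sex or age, and the match is not carried into the analysis.

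The article is a condensed account, and a fuller plan may say more. The choice of tests, however, is stated here and not left open.

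**Conclusion.** The point holds in a limited form. As written, the intervention is tested only by paired t-tests within groups and by unadjusted independent t-tests on an unspecified variable. The paired tests cannot isolate the intervention. The between-group test has a false-positive rate of about 16% to 23% if it uses post values and the groups start 0.2 SD apart. If it uses change, it keeps the nominal 5% under parallel growth, but not under differential growth.

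These rates rest on assumed gaps, drifts and correlations; the article gives none of them, so they illustrate the mechanism and do not forecast this trial. A reader might also conclude that covariate adjustment would make the comparison unconfounded. It would not: group is defined by school year, and the ages of year eight and the controls barely overlap, so any age adjustment leans on an assumed form of the age trend.

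**What to change.** Amend the Data Analysis section as follows.

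- **Test of effect.** For each outcome, one between-group regression of the post value on group, baseline value, sex and maturation stage, reported as an adjusted mean difference with 95% CI.
- **Beside it.** The same model on the change score, with the baseline value left out of the covariates; keeping it in would return the same group coefficient. Report both, because they can differ when groups are non-equivalent.
- **Paired tests.** Label them descriptive.
- **Age trend.** Show year-seven and year-nine control changes separately, so that year eight can be set against both. Adjust for age only as a sensitivity analysis.
- **Conclusions.** State that adjustment does not remove all confounding by school year.

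The cost is a rewritten paragraph and a little more analysis. Baseline values and maturation stage are already collected, and sex should be readily known. No larger sample is needed.

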#### Blood Sampling and Analysis

Following an overnight fast, venous blood samples will be collected between 9.00 and 10.00 a.m. the following day. Participants will be required to assume a seated position for 30 minutes prior to sampling to control for plasma volume shifts [42]. Blood samples will be collected by qualified phlebotomists, and a health professional will be in attendance throughout. Breakfast will be provided to all participants immediately following sampling in the school canteen. Within two hours, all blood samples are to be transported to the laboratory and analysed immediately. Samples will be analysed for total cholesterol (TC), low-density lipoprotein cholesterol (LDL-C), HDL-C, TG, insulin, glucose, high-sensitivity C-reactive protein (hs-CRP), interleukin-6 (IL-6), adiponectin (high molecular weight), and fibrinogen (Fg).

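### Only unadjusted t-tests are named for every variable; if hs-CRP and IL-6 are tested as measured, substantial power may be lost that a log-scale, baseline-adjusted comparison would recover

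*Protocol article*

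**What the plan says.** Data Analysis in the protocol article names one family of tests for all outcomes. Within groups, "Dependant t-tests will be employed to assess differences between measures taken at baseline and post-intervention". Between groups, there are "independent t-tests utilised to detect differences in variables between groups". The significance level is 0.05, with sidedness not given. On sample size, "Power calculations revealed that 100 participants from the exercise group and 60 participants from the control were required to achieve 80% power". The section does not say whether values are analysed as measured or transformed, whether the independent test uses post-intervention values or changes, or whether the baseline value enters the between-group comparison.

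Blood Sampling and Analysis lists triglycerides, insulin, hs-CRP, IL-6 and adiponectin among the fasting variables. Under Primary Objectives, the fourth is: "Improve blood lipid profiles and lower levels of plasma inflammatory markers". That covers triglycerides (as a lipid), hs-CRP and IL-6. Insulin is not named there. No mean, SD, skewness or expected effect is given for any marker.

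**The concern.** A t-test compares arithmetic means. Where a marker's spread is multiplicative, a few pupils with high values dominate both the mean and the SD. The change score suffers most, because its spread grows with a pupil's level. The result is a valid but weak test in which one or two pupils can decide the answer.

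The inflammatory markers belong to a primary objective, and the sample was sized for 80% power. A test well below that could return an inconclusive result when a proportional effect is present. The baseline value is collected on every pupil measured, but the tests named do not use it as a covariate.

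**Working it through.** **1. The plan's own figure.** The 100 + 60 cannot be reproduced, because no outcome, SD or effect is given. Solving backwards, d = (z for alpha + z for 80% power) × √(1/100 + 1/60), where √(0.01 + 0.016667) = 0.1633.
- Two-sided: (1.960 + 0.842) × 0.1633 = 0.457 SD.
- One-sided: (1.645 + 0.842) × 0.1633 = 0.406 SD.

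Two-sided 5% is assumed from here on.

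**2. Fixed effect, change scores.** From the article: n = 100 and 60. Assumed: lognormal marker, pre-post correlation ρ = 0.7 on the log scale, log-SD σ, and the percentage reduction.
- Log change: SD = σ√(2(1 − ρ)) = 0.775σ.
- Log post value adjusted for log baseline: SD = σ√(1 − ρ²) = 0.714σ.
- Approximate power = Φ(|ln(1 − reduction)| / (SD × 0.1633) − 1.96).

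For σ = 0.9 and a 30% reduction (|ln 0.7| = 0.357):
- Log change: SD 0.697, standard error 0.114, ratio 3.13, power Φ(1.17) = 88%.
- Adjusted: SD 0.643, standard error 0.105, ratio 3.40, power Φ(1.44) = 92%.

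Raw-scale power has no such simple form and was simulated. The simulated results were:

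| Assumed σ, reduction | Raw change | Log change | Log, adjusted for log baseline |
|---|---|---|---|
| 0.9, 30% | 56% | 88% | 91% |
| 1.1, 30% | 33% | 71% | 78% |
| 0.5, 20% | 85% | 94% | 97% |

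Taken in that order, the scale accounts for 32, 38 and 9 points and the adjustment for a further 3, 7 and 3. With no effect, rejection rates are near 5% throughout.

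**3. Effect set to give 80% log-scale power.** This separates the loss from the size of effect assumed. The table gives simulated raw-scale power, with 10,000 replicates per row and ρ of 0.5 and 0.7 for the last two columns.

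| Assumed σ | Post values, between groups | Change, between groups | Paired, exercise group |
|---|---|---|---|
| 0.4 | 78% | 71-72% | 74-75% |
| 0.6 | 74% | 62-63% | 67-68% |
| 0.8 | 69% | 53-54% | 59-61% |
| 1.0 | 63% | 43-44% | 50-52% |
| 1.2 | 57% | 34-36% | 40-43% |

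At σ = 0.2 the post-value test has 80% power, so nothing is lost. At 0.4 to 0.5 the cost of the raw scale runs from about 2 points (80 − 78, post values at 0.4) to 9 points (94 − 85, change scores at 0.5). Raw type I error on post values is 4-5%.

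**4. Where the log scale does worse.**
- If the intervention only trims the top quarter of values, log power is 18-19% against 45-70% raw.
- If arithmetic means are equal but log-SDs differ (0.8 v 1.0), the log test rejects 21% of the time against 6% raw, because it compares geometric means.

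**The case against.** The strongest reply is that the article never says the tests are run on measured values. A t-test on logged values is still a t-test, and the choice of scale is commonly left to a full protocol or SAP. This stands. A reader might infer that the plan commits to raw-scale analysis, but the text does not support that, and the silence on scale is not itself an error. What remains is that the article does fix the type of test for every variable, with no baseline covariate, and a stronger analysis is available from the same data.

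A reader might also infer that all the skewed markers lose much of their power. The article gives no skewness for any of them, and the loss runs from nil to about 46 points over the range examined. It is small for mild skew, particularly on post values. The largest losses are for between-group change scores, which the article does not specifically name, although the paired test that it does name also loses heavily at large log-SDs.

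Nor is the log scale free. Step 4 shows cases where it does worse, it changes the quantity estimated, and undetectable values need a rule.

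The assumed 20-30% reductions have no basis in the article, whose Background describes an earlier school programme with no effect on blood lipids, C-reactive protein or fibrinogen. Step 3 therefore does not rely on them.

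Finally, year groups are not randomised. Baseline adjustment improves precision, but it does not remove confounding and it carries its own assumptions if the groups differ at baseline.

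**Conclusion.** The point holds as a worthwhile improvement and not as an error. If the named tests are applied to measured values, a strongly right-skewed marker with a proportional effect loses substantial power: about 33-56% raw against 71-88% on logs for change scores, and 78-91% with the log model adjusted for log baseline (log-SD 0.9 to 1.1, 30% reduction, ρ = 0.7). For log-SD 0.4 to 0.5 the log-scale gain is about 2 to 9 points. That hs-CRP and IL-6 fall in the first group, and triglycerides and insulin in the second, is assumed. Adiponectin was not simulated separately.

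It would be wrong to conclude that the planned tests are invalid, since their type I error is about 5% in these simulations. It would also be wrong to say that the fourth primary objective rests wholly on skewed markers: it covers the wider lipid profile as well, and insulin is not named in it.

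**What to change.** Add to Data Analysis, before results are seen:
- hs-CRP, IL-6, triglycerides, insulin and adiponectin are compared between groups on the log scale, with adjustment for the log baseline value.
- Results are reported as ratios of geometric means with 95% CI.
- Values below the detection limit are handled by a stated rule.

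This takes a few sentences and needs no extra pupils or measurements. The cost is that effects are ratios of geometric means instead of mean differences, and that power can be lower if the effect is confined to the highest values.

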### Intervention

In addition to regular PE lessons (60 min duration), this intervention will aim to increase PA by an additional two hours per week, for 18 weeks. A cross-curricular PA intervention involving all academic subjects termed the 'Activity Knowledge Circuit' will be followed by year eight pupils. These participants will complete 3,200 m of brisk walking during a 60 mins subject (normally classroom based) lesson, where a metronome set at 130 beats per minute will provide a walking speed. Initial pilot work carried out suggests that walking at this intensity for 3,200 m elicits relative oxygen uptake values of 17.0 ± 1.3 ml^-1^kg^-1^min^-1^. Following 18-weeks, performing two intervention lessons per week, it is calculated that energy expenditure will equate to 4039 ± 1387 kcal, leading to a predicted weight loss of 1.2 ± 0.4 lbs, without accounting for confounding variables.

Each intervention lesson will be supervised by a subject teacher, and researcher or member of the PE department to ensure participants walk at the correct speed. Each participant will perform two intervention lessons per week, in addition to two regular PE lessons, thereby increasing activity by two hours a week. Intervention lessons will be integrated into the regular school timetable, and no more than four intervention lessons will be delivered by each curriculum subject during the 18-week period. Short tasks, in line with current curriculum, will be provided by subject teachers for participants to complete at stations set every 400 or 800 m. Participants will therefore, still follow national curriculum whilst exercising at the same time. Tasks are to be designed by teachers to last no longer than 60 seconds at each station. Physical Education lessons are to be implemented as usual.

Normally, all intervention classes will be performed outside on school premises on a pre-determined course. In adverse weather conditions, a course of equal distance has been arranged undercover, again on school premises, so preventing any disruption to the intervention schedule. Participants will wear school uniform whilst taking part, but suitable footwear will be advised. Registers are to be kept during each intervention-led lesson to monitor absentees.

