One of the main limitations to this study includes use of non-randomised sampling, whereby participants from year eight are to be selected to participate in the intervention, with participants from both years seven and nine making up the control group. This is unavoidable due to the manner in which the intervention is to be implemented. Randomly selecting participants from years seven, eight, and nine would lead to children of the same class being divided into intervention and control groups. This would cause too great a disruption to the school's regular curriculum, as well as requiring additional teachers. We considered assigning a whole year group to the intervention, and including maturation matched participants from other year groups as controls, is deemed more practicable. Future studies may look to involve a greater number of schools, allowing the opportunity to randomly assign different schools to an intervention or control group.

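### The between-group t-tests treat pupils as independent although teaching groups are kept intact, so standard errors are too small under any positive class-level correlation; if the 100/60 sample size rests on the same assumption, adjusted power is below 80%

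*Protocol article*

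**What the plan says.** The Data Analysis section of the Protocol article sets out to "compare differences in measured outcomes between pupils assigned to an intervention or control group". Change over time is tested within pupils ("Dependant t-tests will be employed to assess differences between measures taken at baseline and post-intervention"), and the two groups are compared by "independent t-tests utilised to detect differences in variables between groups", at the 0.05 level. No term for class or year group appears. On size, the section says that "100 participants from the exercise group and 60 participants from the control were required" for 80% power. It gives no outcome, effect size, SD, sidedness, ICC or class size.

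The Participants section allocates by school year within one school: year eight receives the intervention, and maturation-matched pupils from years seven and nine are controls. The Discussion explains why pupils were not allocated individually: "Randomly selecting participants from years seven, eight, and nine would lead to children of the same class being divided into intervention and control groups". The Intervention section places the walks inside the ordinary timetable: "Each intervention lesson will be supervised by a subject teacher, and researcher or member of the PE department". The Measurements section places pre- and post-intervention measurement in PE lessons for both groups. The limitations paragraph of the Discussion names non-random selection but does not mention correlation between pupils taught together.

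**The concern.** An independent t-test takes each pupil as a separate piece of information. Here, pupils in a teaching group walk in the same lessons, pause for the same teacher-set tasks, miss or complete the same sessions and may be tested in the same PE lesson. The last matters most for the shuttle run, which depends on effort and encouragement on the day. Such pupils will tend to resemble each other. The test then understates the standard error, gives intervals that are too narrow and rejects a true null hypothesis more than 5% of the time.

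The choice of test is stated in the article, so this is not a detail left to an unseen analysis plan. At stake is a false claim of benefit on one or more of the many outcomes under the primary objectives, and a power statement that may not survive a correct analysis.

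**Working it through.** **1. The plan's own figure.** The 100/60 sample size cannot be reproduced, because no effect size, SD or outcome is given. It can only be solved backwards, assuming independent pupils and a two-sided 5% test:

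d = (1.960 + 0.842) × √(1/100 + 1/60) = 2.802 × 0.1633 = 0.457 SD (0.460 by noncentral t with 158 df; 0.406 if one-sided).

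This d follows from the independence assumption and is not a figure in the article. With other true effects, 100/60 would give 45% power at 0.3 SD, 69% at 0.4 SD and 86% at 0.5 SD.

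**2. Inputs.** From the article: 100 and 60 pupils, 80% power, significance level 0.05. Assumed, because the article is silent: ICC of 0.02, 0.05 or 0.10; and either 20 to 25 analysed pupils per class in both arms, or 20 exercise and 6 control pupils per class. The second pattern is plausible because only about 60 matched controls are drawn from two year groups.

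**3. Formulae.**
- Equal class size m: DE = 1 + (m − 1) × ICC.
- Unequal class sizes: DE = [(1 + 19 × ICC)/100 + (1 + 5 × ICC)/60] ÷ (1/100 + 1/60).
- True error of the unadjusted test: 2 × [1 − Φ(1.96/√DE)].
- Power of a correctly adjusted test at d = 0.457: Φ(2.802/√DE − 1.96).

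Worked example, m = 20 and ICC = 0.05: DE = 1 + 19 × 0.05 = 1.95 and √DE = 1.40. The error is 2 × [1 − Φ(1.40)] = 16%. Power is Φ(2.802/1.40 − 1.96) = Φ(0.05) = 52%.

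Worked example, unequal classes and ICC = 0.05: (1.95/100 + 1.25/60)/0.02667 = 0.04033/0.02667 = 1.51. The error is 11% and power is 62%.

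**4. Results.**

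| Pupils per class (exercise, control) | ICC | DE | Error of planned t-test | Power of adjusted test |
|---|---|---|---|---|
| 20, 20 | 0.02 | 1.38 | 10% | 66% |
| 20, 20 | 0.05 | 1.95 | 16% | 52% |
| 20, 20 | 0.10 | 2.90 | 25% | 38% |
| 25, 25 | 0.02 | 1.48 | 11% | 63% |
| 25, 25 | 0.05 | 2.20 | 19% | 47% |
| 25, 25 | 0.10 | 3.40 | 29% | 33% |
| 20, 6 | 0.02 | 1.21 | 7% | 72% |
| 20, 6 | 0.05 | 1.51 | 11% | 62% |
| 20, 6 | 0.10 | 2.03 | 17% | 50% |

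**5. The last two columns describe different tests.** The error rates belong to the planned t-test, and the power figures to a test with correct standard errors. At d = 0.457 the planned t-test would still reject about Φ(0.842/√1.38) = 76% of the time at DE 1.38, and about 68% at DE 3.40. Its main fault is false positives, not lost rejections.

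**6. Few classes.** The power column uses the normal distribution. With 160/20 = 8 classes, a t reference on 8 − 2 = 6 df lowers power at ICC 0.05 from 52% to about 40%.

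**The case against.** The strongest objection concerns power. A reader might infer that the real power is below 80% and that the 100/60 figure ignored clustering. The article does not show either. It gives no method or inputs, so an allowance for clustering cannot be ruled out, and an argument from 0.457 SD alone is circular. This objection stands, and the power point must remain conditional. The pupil-level t-tests make independence the likely basis, but no more than that.

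The mechanism also has limits. The metronome and the walking distance are the same for all of year eight, so they create no differences between classes. There is no single class teacher either: two lessons a week for 18 weeks is 36 lessons, and with at most four per subject at least 36/4 = 9 subjects take part. The article does not say that teaching groups stay the same across subjects or coincide with PE groups. The shared-session argument does not reach the food diary, which is completed at home. These points weaken the case for a large ICC and show that the class needs defining. They do not make independence a safe assumption.

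The size depends on how many controls share a class, and sparse control classes reduce it, as the last three rows of the table show. The t-test also ignores the maturation matching. If matching induces positive correlation between the groups, it could offset part of the error, but nothing in the article shows that it would cancel it.

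Finally, the Discussion already concedes non-random allocation by year. A reader might take a class term as a cure for that. It is not, because the whole intervention arm is one school year. This calls for caution in the conclusions and does not justify leaving standard errors too small.

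**Conclusion.** The concern holds for the analysis and holds conditionally for power. The stated independent t-tests do not fit a study delivered through intact teaching groups and measured in PE lessons. With any positive class-level correlation their standard errors are too small. Under assumed ICCs of 0.02 to 0.10, the true error of the nominal 5% test is about 10% to 29% with 20 to 25 pupils per class in both arms, and about 7% to 17% with 20 exercise and 6 control pupils per class.

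If the 100/60 calculation assumed independent pupils, a correctly adjusted analysis has less than 80% power for its target effect: about 33% to 66% and 50% to 72% in the same two cases, and lower still once few classes are allowed for. The stated 80% can be neither confirmed nor refuted from the article.

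**What to change.** - Define the cluster (form or PE class) and record it for every pupil in both arms. The registers described in the Intervention section cover intervention lessons only, so the class of each control pupil has to be collected separately.
- Replace the independent t-test with a baseline-adjusted model that has a random intercept for class, using Kenward-Roger or Satterthwaite degrees of freedom because classes are few.
- Restate the power calculation with its outcome, effect size, SD, assumed ICC and class size.
- State in the conclusions that no model can separate the effect of the intervention from that of being in year eight.

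Delivery of the intervention does not change. The cost is one extra data item per pupil, including controls, together with wider intervals and probably a lower stated power.
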